### Consent or assent

The informed consent form is completed online by all study participants.

### Inclusion and exclusion criteria

The inclusion criteria in this study are as follows: willingness to participate in the study, access to the internet, and having the skills to use the internet. The exclusion criteria include the following: having a second job, suffering from congenital musculoskeletal disorders, history of surgery in the neck region, history of neck vertebral fractures and pathologic neck pain, and medical prohibition in doing neck preventive behaviors.

The main purpose of this study is to promote preventive neck pain behaviors, so the first phase of the study identifies the behavioral factors that cause neck pain to address them through designing and implementing proper educational intervention based on the health belief model. The findings of this stage are obtained through semi-structured interviews based on the health belief model which clarify the behavioral factors affecting neck pain. Based on HBM, these factors might be included perceived sensitivity, perceived severity, perceived benefits, perceived barriers, cues to action, and self-efficacy [34].

### Designing and development of educational intervention

#### Educational intervention content

Definition of occupational neck pain and its causes, benefits of healthy preventive behaviors, strategies to deal with barriers towards doing neck pain prevention behaviors, improving self-efficacy in adopting and performing neck pain preventive behaviors, stressors in the workplace and their effects on neck pain preventive behaviors, stress management techniques, effective communication, angry management skills, excitement management skills, ergonomic principles on neck pain prevention, correct movements that reduce neck pain, stretching movements that strengthen neck muscles, sleeping properly, proper sitting and standing, correct posture while working with computer/mobile phone, and all skills regarding doing all daily activities in correct posture are included in intervention content. Before implementing intervention, the prepared educational contents are reviewed by experts in the fields of health education/health promotion, occupational health, ergonomics, and physiotherapy and also psychology in terms of scientific and appropriateness validity. Moreover, before presenting the educational contents to the participants in intervention group, the contents are examined in terms of simplicity, clarity, comprehensibility and appropriateness by a sample of teachers who are similar to target group of the study. Moreover, accuracy of their mobile device and internet access will be checked during educational intervention transferring.

#### Implementation of intervention

Participants can communicate with the researcher by email and phone call. The intervention group will receive training in the form of webinars, group discussions, questions and answers, videos, animations, posters, pamphlets, and infographics. The procedure of teacher training is supervised by the researcher. The training will be provided to the intervention group through social media for 1 month. After, the reminder training will be provided to the intervention group for 3 months. During this period, the control group will not receive any intervention. However, the training package will be provided to the control group after the study is finished. Although there is no auditing plan in this study, if there are any participants with this problem, he/she will be excluded from the study.

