### Sampling

At this stage, a list of all 26 schools in district 19 of education ministry in Tehran will be prepared. From the schools, people are randomly selected and then randomly divided into two groups of intervention and control. The intervention group receives a training program while the control group does not receive any training program. Participants are evaluated in three time points of before the intervention, 1 and 3 months after the intervention. The study setting will be public schools in the 19th district of education ministry in Tehran city of Iran. The schools in this district are located in center of city that is almost similar to majority of other schools. Participants are teachers of junior high school.

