### Calculating sample size

Based on the similar existed evidence (21) and considering the 95% confidence level and 80% test power, the number of necessary samples for each group (intervention and control) according to Pocock formula is 63 people which plus 10% for dropout would be of 73 people in each group finally. For randomization, first, a list of teachers’ telephone numbers with a specific code is prepared, and the codes are poured into a bag and randomly divided into two groups of intervention and control. This study is a double-blind study, so the researcher and participants are not aware of about the grouping of individuals.

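### An exclusion rule with no defined trigger can remove teachers after randomisation, and on some readings in one arm only

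*Protocol article*

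**What the plan says.** Under Sampling, "people are randomly selected and then randomly divided into two groups of intervention and control". Training comes afterwards. Under Implementation of intervention, the intervention group is trained for one month and then receives reminders for three months. Of the controls the article says: "During this period, the control group will not receive any intervention". They get the package once the study is over. The same paragraph ends with a sentence that first concedes that there is no auditing plan and then states that "if there are any participants with this problem, he/she will be excluded from the study". Nothing earlier in the paragraph is called a problem.

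The nearest check on participants is at the end of Educational intervention content: "accuracy of their mobile device and internet access will be checked during educational intervention transferring". Eligibility already requires "access to the internet, and having the skills to use the internet" (Inclusion and exclusion criteria). The same section lists exclusions such as earlier neck surgery, vertebral fracture, pathologic neck pain and medical prohibition of the preventive behaviours.

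**The concern.** A randomised comparison is protected only while the groups compared are the groups that were drawn. This rule takes people out of the study, not merely out of training, so their one- and three-month questionnaires would not be collected. It does so for a reason that is not stated and may arise or be noticed only after allocation. Because the trigger is undefined, who leaves is at the researcher's discretion.

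If those who leave differ in behaviour score from those who stay, and leave more often from one arm, the difference in means no longer estimates the effect of the training alone. Teachers with poor connections or little engagement may well score lower. Removing them from the intervention arm would then favour the intervention even if the training did nothing. A later analysis plan could define an analysis set, but it could not recover outcomes that were never collected.

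**Working it through.** **1. Reading the rule.** The plan gives no number for such removals, so there is no figure to reproduce. The possible meanings of the trigger, set against the text, are:

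| Reading | Support in the article | Arm affected |
|---|---|---|
| Device or internet failure | Check made while content is transferred (Educational intervention content); controls receive no content | Intervention only |
| Control exposed to the training | A sentence on controls receiving nothing comes shortly before the rule | Control only |
| Exclusion criterion or neck pain found late | Inclusion and exclusion criteria; the phase 1 text in Methods/design uses the same two words for neck pain; the rule names no arm | Possibly both |

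On all three, removal depends on an event or discovery after allocation.

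**2. Inputs for an illustration.**
- From Calculating sample size: "considering the 95% confidence level and 80% test power", and the number per group "according to Pocock formula is 63 people".
- Arm size used: 63/(1 − 0.10) = 70. The article states 73; results at 73 are given below.
- Implied planned effect, two-sided test assumed: d = √(2/63) × (1.960 + 0.842) = 0.50 SD. The article gives no effect size or SD.
- Assumed, not in the documents: fraction removed f = 5% to 15% of one arm; correlation r = 0.2 to 0.5 between the removal factor and the outcome; the lowest on that factor are removed; no true effect.

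**3. Formulas.** The mean of those who remain shifts by b = r × φ(z_f)/(1 − f), where φ is the normal density and z_f the f-quantile. With n₁ left in the affected arm, SE = √(1/n₁ + 1/70). The two-sided type I error is 1 − Φ(1.96 − b/SE) + Φ(−1.96 − b/SE).

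- Low end, f = 5%, r = 0.2: b = 0.2 × 0.1031/0.95 = 0.022 SD. With 4 removed, n₁ = 66, SE = 0.172, type I error 5.2%.
- Middle, f = 10%, r = 0.5: b = 0.5 × 0.1755/0.90 = 0.098 SD. With 7 removed, n₁ = 63, SE = 0.174, type I error 8.7%.
- High end, f = 15%, r = 0.5: b = 0.5 × 0.2332/0.85 = 0.137 SD. With 10 removed, n₁ = 60, SE = 0.176, type I error 12.2%.

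A simulation with 20,000 runs per case (70 against 70, whole persons removed, t test) gives 0.024 SD and 5.4%, 0.096 SD and 9.0%, and 0.130 SD and 12.0%. The last bias is a little below the formula because 10 of 70 is 14.3%, not 15%. With 73 per arm the high end is 0.136 SD and 13.2%.

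**4. Cross-check by a second route.** If those removed average g SD below those who remain, the shift is b = f × g. With 73 per arm, f = 5% to 15% and g = 0.25 to 1.0 (assumed), b runs from 0.05 × 0.25 = 0.0125 to 0.15 × 1.0 = 0.15 SD. Type I error runs from 5.1% to 14.0%. This is the same order.

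**5. Scale.** Against the implied 0.50 SD, 0.02 to 0.13 SD is 4% to 26% of the planned effect. Power is not the issue: with 10% lost from one arm of 73 it is still about 83.5%.

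**6. Removal in both arms.** The bias in the difference is b(intervention) − b(control). If the fraction removed and its link with the outcome are alike in both arms, this is zero.

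**The case against.** The strongest case against is that nobody can tell what the sentence means. It opens with a remark on auditing and may be a garbled answer to a question about that. It mentions neither devices nor control exposure, names no arm and gives no time of detection. The device check stands under another heading and follows a sentence about a pilot sample of teachers. It does not say that anyone who fails is removed; it may exist only so that access can be put right.

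This stands, and it limits the point. A reader might infer that the rule strikes one arm only and so favours the intervention. The documents do not establish that, because the reading that covers both arms is at least as well supported. A reader might also quote type I errors above 20%. In the same simulation, 10% removed with a correlation of 1 gives 22.5%, and 15% gives 35.9%. Those figures require the removal factor to predict the behaviour score perfectly, which nothing supports. Since internet access and skill are entry criteria, fewer than 5% might be removed for that reason. Nor is it a fault in itself that the article does not state analysis as randomised; a condensed article commonly leaves that to the analysis plan.

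The objection does not remove the core. The article states a positive instruction to exclude, places it in the delivery of the intervention, and nowhere reverses it. An unclear trigger leaves more to discretion after allocation, not less.

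**Conclusion.** The point holds as an undefined exclusion that can act after randomisation. That it acts in one arm, or in a known direction, is possible but not shown. On the device and control-exposure readings one arm is affected; on the late-discovery reading both may be.

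The size cannot be derived from the documents. Under the stated assumptions (5% to 15% of one arm, correlation 0.2 to 0.5, no true effect, 70 per arm), bias is about 0.02 to 0.13 SD and type I error about 5% to 12%. With similar removal in both arms, no net bias need arise. The low end is negligible; the high end is about a quarter of the implied planned effect. The sentence should be corrected. Confidence that it is defective is good; confidence in any particular size is low.

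**What to change.** - **Define the trigger.** State what the problem is, when it is looked for, and that the same procedure applies in both groups.
- **Check before the draw.** Confirm working device and internet access in both groups before randomisation. Access and skill are already inclusion criteria, but the stated check is made during delivery and none is described for controls, so this is a small addition.
- **Replace the exclusion.** Suggested wording: *Every randomised teacher is asked to complete the one- and three-month questionnaires and is analysed in the allocated group, whether or not training was received or stopped.*
- **Record, do not remove.** Log delivery failures in the intervention group, and add one question on exposure to the training material to the follow-up forms. Use both in a sensitivity analysis only.
- **If a medical exclusion is meant,** reconcile the sentence with the section on inclusion and exclusion criteria, and keep stopping of training separate from removal from follow-up and analysis. Which clinical rule applies is for the investigators to settle.

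The cost is a change of wording, an earlier check in both groups and one question. The statistical downside is a somewhat diluted effect estimate, since teachers who did not receive the training stay in their arm. No extra participants are needed.

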#### Questionnaire used in this study

The main outcome of the study is promoting of neck pain preventive behaviors that will be assessed using a researcher-made questionnaire. Data collection instrument is a researcher-made questionnaire that is completed and collected in three stages. Therefore, before the intervention, 1 month after the intervention and 3 months after the intervention, the questionnaire is presented to the intervention and control groups for completion. The data obtained in three stages in both groups are analyzed to determine whether the educational intervention is effective in promoting neck pain preventive  behaviors in teachers.

#### Scoring questionnaire

Questionnaires are completed anonymously to gain participants’ trust in the intervention. This questionnaire has different domains of HBM such as knowledge, perceived sensitivity, perceived severity, perceived barriers, perceived benefits, and cues to action, self-efficacy, and behavior. Knowledge questions have the Likert form with three-part spectrum as true (with score 2), no idea (with score 1), wrong (with score 0), and domain questions of perceived sensitivity, perceived intensity, perceived barriers, perceived benefits, self-efficacy, and cues to action which have 5-part Likert spectrum form like completely agree with score 5, agree with score 4, no idea with score 3, disagree with score 2, and completely disagree with score 1. Behavior questions are considered as a five-part Likert scale: never with score 1, rarely with score 2, sometimes with score 3, often with score 4, and always with score 5. This questionnaire measures the variables of knowledge, perceived threats, self-efficacy, reinforcing factor, and barriers towards behavior doing. A higher score in each area of the questionnaire indicates a better situation.

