**Fig. 1 Fig1:**
[figure not shown]
The constructs of health belief model

Accordingly, the first phase of this research project was done through interviews with the teachers based on this model, and the results clarified that they did not perceive the severity of neck pain consequences. Furthermore, they did not consider themselves as susceptible individuals for neck pain if they would not comply with preventive behaviors. On the other hand, they did not understand the benefits of neck pain preventive behaviors and so they mentioned many barriers including being unskilled to do these preventive behaviors. In other words, they lacked sufficient self-efficacy. Therefore, it was concluded that health belief model would be a proper model which possibly can overcome these causative factors of not doing preventive behaviors by teachers.

Therefore, according to address these limitations, this protocol aims to develop an intervention based on the health belief model in social media context in order to promote preventive behaviors among the school teachers.

*To achieve the overall goal, three following phases needed to be considered:*

Phase1: Carrying out a qualitative study to determine the leading factors influence doing neck pain preventive behaviors and domain/item generation of researcher-made questionnaire

Phase 2: Psychometrics of the developed questionnaire

Phase 3: Designing and implementation of an educational intervention based on the health belief model in the context of social networks to adopt behaviors that to reduce neck pain in teachers

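### Perceived barriers is coded agree = 5 with no reversal, so under the higher-is-better rule a successful fall in barriers reads as a worsening

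*Protocol article*

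**What the plan says.** The Scoring questionnaire section of the protocol article fixes three things that bear on this point.

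- **Which domains share the agreement scale.** Perceived barriers is named alongside the favourable constructs: "domain questions of perceived sensitivity, perceived intensity, perceived barriers, perceived benefits, self-efficacy, and cues to action which have 5-part Likert spectrum form".
- **How the responses are coded.** One set of codes serves all of these domains: "completely agree with score 5, agree with score 4, no idea with score 3, disagree with score 2, and completely disagree with score 1".
- **How a score is to be read.** One rule covers the whole instrument: "A higher score in each area of the questionnaire indicates a better situation". No domain is excepted, and reverse coding is not mentioned.

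The same section describes what the barriers domain captures as "barriers towards behavior doing". Two other places show which direction is favourable. In the Background, in the text after Fig. 1, the interviewed teachers did not see the benefits of prevention, and "they mentioned many barriers including being unskilled to do these preventive behaviors"; the model was chosen because it might overcome such causes. Under Educational intervention content, the training includes "strategies to deal with barriers towards doing neck pain prevention behaviors".

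**The concern.** The article does not leave scoring open. It states the codes and the direction of interpretation, and for one named domain the two do not fit together. Agreeing that barriers exist earns the highest score, and the highest score is then declared the best situation. Yet the programme is meant to help teachers deal with barriers, so a programme that works should produce less agreement.

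What is at stake is the reading of the barriers results. The Data monitoring section plans a t test between groups, paired t tests within groups for two time points, and ANOVA within groups for three time points. If the scoring rule is followed as written, an effective programme could be reported as having worsened perceived barriers, or a rise in barriers could be reported as a benefit. Barriers is one of the constructs of the model on which the intervention is built, so the error would also distort any account of whether the programme worked in the way the model predicts.

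**Working it through.** The article gives no numerical result on this point, so there is no figure to reproduce. The check applies the stated codes to a barrier item and compares the sign of the change with the stated rule.

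**Inputs**

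- Codes (Scoring questionnaire): completely agree 5, agree 4, no idea 3, disagree 2, completely disagree 1.
- Direction rule (same section): higher is better in every area.
- Favourable direction for barriers (Background after Fig. 1; Educational intervention content): fewer perceived barriers.
- Assumption: the items are worded as barriers, so agreement means that a barrier is present. The items are not shown.

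**Step 1: as coded.** A teacher agrees with a barrier item before the programme and disagrees afterwards.

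Change = after - before = 2 - 4 = -2.

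The barrier has receded, but the score has fallen, and the rule reads this as worse.

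**Step 2: reverse-coded.** Let y = 6 - x. The codes 5, 4, 3, 2, 1 become 1, 2, 3, 4, 5.

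Change = (6 - 2) - (6 - 4) = 4 - 2 = +2.

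The same answers now give a rise, which agrees with the rule.

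**Step 3: effect on the planned tests.** Let M be a respondent's mean item score on the barriers domain, so the reversed score is 6 - M.

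- Between groups: (6 - mean M, intervention) - (6 - mean M, control) = -(mean M, intervention - mean M, control). The standard deviation is unchanged, because subtracting from a constant does not alter spread. The t statistic therefore changes sign but not size, and the two-sided p value is the same.
- Within a group, two time points: each paired difference changes sign, with the same consequence.
- Within a group, three time points: the F statistic is built from squared deviations and is unchanged. It carries no sign, so the direction comes entirely from reading the means.

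A sum of k items behaves in the same way, with 6k - sum in place of 6 - M.

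**Step 4: reach.** The Questionnaire used in this study section names preventive behaviour as the main outcome. Behaviour has its own frequency scale, from never = 1 to always = 5, on which a higher score for a preventive behaviour is favourable. The conflict found here does not touch that scale.

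**The case against.** The strongest reply is that the conflict depends on items that nobody can see. If every barrier item were worded as the absence of a barrier, codes and rule would agree. The codes might also describe only the response format, with the direction rule applying to domain scores after a recoding that the article does not mention. A condensed article can reasonably leave the item-level key to the full protocol or the instrument. The intended direction is also clear from the rest of the text, and a recode can be applied at any time without loss of data.

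Part of this stands. The wording of the items is an assumption, and the consequence is limited and reversible. But nothing in the article says that the barrier items are inverted or recoded. The point is not that an item key is missing; it is that two scoring statements the article does make disagree for a domain it names. Even on the favourable reading, a sentence is needed so that the sign can be interpreted.

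A reader might infer more from the same section, and the document does not support it:

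- **A diluted total score.** If the domains were summed, an unreversed barriers domain would offset gains elsewhere. The article defines no total across domains, so no such loss can be claimed.
- **Miscoded knowledge items.** The knowledge codes, "true (with score 2), no idea (with score 1), wrong (with score 0", could be taken as crediting the response 'true' whatever the right answer is. They can equally mean correct and incorrect, which would be sound scoring.
- **A weakened main outcome.** Scoring 'always' as 5 would be wrong for an item describing a high-risk habit. Nothing says that the behaviour domain contains such items, and the outcome is described as preventive behaviour.

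**Conclusion.** The point holds for the direction of the perceived-barriers domain and for nothing wider. With items worded as barriers, the stated codes and the stated rule give a wrong-signed interpretation: an improvement of two response categories on an item is read as a loss of 2 points instead of a gain of 2. The magnitude of every barriers comparison and its two-sided p value are unaffected, so the error would pass through the analysis unnoticed and surface only in the conclusion drawn.

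This should be corrected, but it does not threaten the trial's main result. Barriers is not the main outcome. The conclusion rests on one assumption, the wording of the items, and would fall away if all of them turned out to be phrased as the absence of barriers.

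**What to change.** In the Scoring questionnaire section, add one sentence that does one of the following:

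- states that perceived-barriers items are reverse-coded as 6 minus the score before the domain score is formed, so that higher means fewer barriers; or
- keeps the codes as they are and excepts barriers from the higher-is-better rule, stating that a lower barriers score is favourable.

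If the items are in fact worded as the absence of barriers, say so instead; no recoding is then needed. Whichever applies, settle it before the data are analysed and repeat the direction in any table that reports the domain. The cost is a sentence and, for the first option, one recode step in SPSS. No new data are needed, and the sample size and planned tests do not change.
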